### 3. First IRIS event over the first 6 months after randomisation

The criteria for neurological IRIS diagnosis is defined in the study protocol
^
1
^. The neurological IRIS rate will be defined as the number of IRIS events divided by the observed person-time of follow-up in each treatment group. A description of all the IRIS events will be given, describing how they met the IRIS diagnostic criteria.

The number of IRIS events in each group will be summarised. Death will be interpreted as a competing risk. Analyses will additionally be performed in the subgroups defined by TBM MRC grade, diagnostic category, ART status at enrolment, time from randomisation to start of ART, and baseline CD4 count.

### 4. AIDS-defining event or death over the first 12 months after randomisation

Acquired immunodeficiency syndrome (AIDS)-defining illnesses will be defined as per the World Health Organisation (WHO) classification. WHO define AIDS as a clinical diagnosis (presumptive or definitive) of any stage 4 HIV condition
^
13
^.

### 5. HIV-associated malignancy over the first 12 months after randomisation

HIV-associated malignancy is defined as new diagnosis of one or more of the three major HIV-associated malignancies; Kaposi sarcoma, high grade B-cell non-Hodgkin lymphoma or invasive cervical cancer.

The number of HIV-associated malignancy events in each group will be summarised. Death will be interpreted as a competing risk. Analyses will additionally be performed in the subgroups defined by ART status at enrolment.

### 6. Use of open-label corticosteroid treatment for any reason, and at any time, after randomisation

The number of open-label corticosteroid treatment events in each group will be summarised. The reasons for corticosteroid treatment will be listed. Death will be interpreted as a competing risk.

### 7. Requirement for shunt surgery by 12 months

The number of shunts performed in each group will be summarised. Death will be interpreted as a competing risk.

### Adverse events until 12 months

Serious adverse events (SAE) are defined in the study protocol
^
1
^. SAE will be sub-grouped into categories. SAE will be grouped and graded as per Common Terminology Criteria for Adverse Events (CTCAE)
^
14
^.

The number of patients with any serious adverse event will be summarised and compared between the two treatment arms based on the chi-squared test, or Fisher’s exact test in case the expected count under the null hypothesis in at least one of the cells is smaller than one
^
15
^. Specific adverse events will be summarised, but not formally compared. The total number of serious adverse event episodes per patient will also be summarised and informally compared based on a quasi-Poisson regression model with treatment as the only covariate.

The following subgroups of adverse events will also be separately summarised: clinical grade 3&4 adverse events; serious adverse events possibly, probably, or definitely related to the study drug; adverse events leading to TB treatment or ARV interruptions. Grade 3&4 laboratory abnormalities will be summarised in the same way as clinical adverse events. Adverse events will be shown as per
Table 6–
Table10.

**Table 6a. T6:** Summary of serious adverse events.

Characteristic	Dexamethasone (N=XX)		Placebo (N=XX)		Comparison (p-value)
	N.pt	N.ae	N.pt	N.ae	
Any selected serious adverse event	XX (XX%)	XX	XX (XX%)	XX	X.XX
Serious adverse events of all types	XX (XX%)	XX	XX (XX%)	XX	X.XX

N.pt = the number of patients with at least one serious adverse event (% of all patients receiving the same intervention) N.ae = the total number of episodes of that particular serious adverse event

**Table 6b. T6b:** Summary of serious adverse events, shown by reasons for which they were considered serious, not shown by study arm.

	Causes death (N=XX)	Life threatening event * (N=XX)	Hospitalisation of prolongation of hospitalisation (N=XX)	Persistent or significant disability/ incapacity ** (N=XX)	Congenital anomaly/ birth defect (N=XX)	Important medical event which may jeopardise the patient and/or require intervention (N=XX)
	n Summary statistic	n Summary statistic	n Summary statistic	n Summary statistic	n Summary statistic	n Summary statistic
Name of event	XX (XX%)	XX (XX%)	XX (XX%)	XX (XX%)	XX (XX%)	XX (XX%)

* Subjects were at immediate risk of death at the time of the event; it does not refer to an event which hypothetically might have caused death if it were more severe ** A substantial disruption of a person's ability to conduct normal life functions N is the number of all patients, n is the number of patients with a non-missing value Summary statistic is absolute count (%) for categorical variable(s).

**Table 7. T7:** Summary of serious adverse events possibly, probably, or definitely related to the study drug.

Characteristic	Dexamethasone (N=XX)		Placebo (N=XX)		Comparison (p-value)
	N.pt	N.ae	N.pt	N.ae	
Any selected serious adverse event possibly, probably, or definitely related to the study drug	XX (XX%)	XX	XX (XX%)	XX	X.XX
Serious adverse events of all types possibly, probably, or definitely related to the study drug	XX (XX%)	XX	XX (XX%)	XX	X.XX

N.pt = the number of patients with at least one serious adverse event (% of all patients receiving the same intervention) N.ae = the total number of episodes of that particular serious adverse event

**Table 8. T8:** Summary of clinical grade 3&4 adverse events.

Characteristic	Dexamethasone (N=XX)		Placebo (N=XX)		Comparison (p-value)
	N.pt	N.ae	N.pt	N.ae	
Any selected clinical grade 3&4 adverse event	XX (XX%)	XX	XX (XX%)	XX	X.XX
Clinical grade 3 adverse events of all types	XX (XX%)	XX	XX (XX%)	XX	X.XX
Clinical grade 4 adverse events of all types	XX (XX%)	XX	XX (XX%)	XX	X.XX
Clinical grade 3&4 adverse events of all types	XX (XX%)	XX	XX (XX%)	XX	X.XX

N.pt = the number of patients with at least one adverse event (% of all patients receiving the same intervention) N.ae = the total number of episodes of that particular adverse event The ‘clinical grade 3&4 adverse events of all types’ grouping will include only the group of adverse events that cannot be separated into grades 3 or 4 (recorded as ‘grade 3 or 4’ at the beginning of the trial). These events will not also be represented in the above ‘grade 3’ and ‘grade 4’ rows.

**Table 9. T9:** Summary of adverse events leading to TB treatment or antiretroviral (ARV) interruptions.

Characteristic	Dexamethasone (N=XX)		Placebo (N=XX)		Comparison (p-value)
	N.pt	N.ae	N.pt	N.ae	
Any selected adverse event leading to TB treatment or antiretroviral interruptions	XX (XX%)	XX	XX (XX%)	XX	X.XX
Adverse events of all types leading to TB treatment or antiretroviral interruptions	XX (XX%)	XX	XX (XX%)	XX	X.XX

N.pt = the number of patients with at least one serious adverse event (% of all patients receiving the same intervention) N.ae = the total number of episodes of that particular serious adverse event

**Table 10. T10:** Summary of Grade 3&4 laboratory abnormalities.

Characteristic	Dexamethasone (N=XX)		Placebo (N=XX)		Comparison (p-value)
	N.pt	N.ae	N.pt	N.ae	
Any selected grade 3&4 laboratory abnormalities	XX (XX%)	XX	XX (XX%)	XX	X.XX
Grade 3&4 laboratory abnormalities of all types	XX (XX%)	XX	XX (XX%)	XX	X.XX

N.pt = the number of patients with at least one serious adverse event (% of all patients receiving the same intervention) N.ae = the total number of episodes of that particular serious adverse event

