## Background and rationale for study

The ACT HIV clinical trial is a randomised double-blind placebo-controlled trial of adjunctive dexamethasone for the treatment of tuberculous meningitis (TBM) in HIV-positive adults. TBM is the most severe form of tuberculosis, with mortality approaching 50% in people living with HIV
^
2–
5
^ despite the best available appropriate anti-TB chemotherapy.

TBM develops when
*Mycobacterium tuberculosis*, initially acquired via the respiratory route, disseminates via the blood to form a secondary focus in the brain. Rupture of this secondary focus into the subarachnoid space results in TBM, with the consequent host inflammatory response being important for bacterial killing, but also responsible for the pathological complications and often-fatal consequences of the infection.

Adjunctive anti-inflammatory corticosteroid therapy, which may control excessive host inflammation, has long been considered to have a role in TBM treatment
^
6
^. In 2004, a landmark clinical trial in Vietnam demonstrated that a 6–8 week (duration dependent on Modified Research Council [MRC] TBM severity grade) tapering course of dexamethasone reduced mortality in adults and adolescents with TBM
^
4
^. In this study, only 98/545 (18.0%) individuals were HIV positive, which was too small to determine if dexamethasone benefited this important sub-group of patients. No other trials have been published since 2004 that examine whether corticosteroids improve outcomes from TBM in HIV-positive adults.

How dexamethasone might confer its clinical benefit on those with TBM remains uncertain. A recent study of cerebrospinal fluid (CSF) cytokines in TBM suggested that HIV-positive individuals have higher cytokine concentrations than HIV-negative individuals
^
7
^. Whether adjunctive dexamethasone is more or less likely to be beneficial in HIV-positive individuals with TBM is not known. There are an estimated 100,000 cases of TBM globally each year
^
8
^, many associated with HIV. Clinical trial data are required to provide an evidence base for adjunctive dexamethasone in HIV-positive individuals with TBM, and to guide clinical practice.

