## Structure and status of trial

The ACT HIV trial commenced recruitment on 25
^th^ May 2017. By April 29
^th^ 2021, the predefined sample size of 520 adults with TBM and HIV co-infection had been enrolled from four hospitals in Vietnam and Indonesia: the Hospital for Tropical Diseases (HTD) and Pham Ngoc Thach Hospital for Tuberculosis and Lung Disease (PNT) in Ho Chi Minh City, Vietnam, and Cipto Mangunkusumo Hospital and Persahabatan Hospital in Jakarta, Indonesia. Detailed enrolment criteria for ACT HIV, including consent and ethical approvals, are described in the published trial protocol
^
1
^.

Once enrolled, study participants were randomised to dexamethasone or placebo (a double-blinded allocation), with this intervention termed ‘study drug’. Randomisation was stratified by TBM MRC severity score and by hospital. Participants with MRC grade 1 TBM received a 6-week tapering course of study drug, whereas participants with MRC grades 2 or 3 received an 8-week tapering course of study drug. Study drug regimens are shown in
Table 1. Participants then underwent clinical assessments at baseline, at days 3, 7, 10, 14, 21, and 30, monthly until month 12, and then 3-monthly until 24 months. Baseline assessment included blood tests, chest X-ray, lumbar puncture, and brain imaging.

**Table 1. T1:** Study drug treatment regimen following randomisation.

	MRC Grade I Daily dexamethasone dose/route	MRC Grades II and III Daily dexamethasone dose/route
Week 1	0.3 mg/kg/24 hrs IV	0.4 mg/kg/24 hrs IV
Week 2	0.2 mg/kg/24 hrs IV	0.3 mg/kg/24 hrs IV
Week 3	0.1 mg/kg/24 hrs IV	0.2 mg/kg/24 hrs IV
Week 4	3mg/24 hrs oral	0.1 mg/kg/24 hrs IV
Week 5	2mg/24 hrs oral	4 mg/24 hrs oral
Week 6	1 mg/24 hrs oral	3 mg/24 hrs oral
Week 7	Stop	2 mg/24 hrs oral
Week 8		1 mg/24 hrs oral

IV=intravenous. MRC=Modified Research Council.

ACT HIV has numerous sub-studies, as described in the protocol
^
1
^. Key follow up outcomes include survival, disability, and severe adverse events; especially neurological events, events requiring corticosteroids, HIV-associated complications (malignancies, immune reconstitution inflammatory syndrome [IRIS]), and adverse events considered related to dexamethasone.

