### Secondary endpoints

The secondary endpoints of the ACT HIV trial are as follows:

1. Neurological disability at 12 months from randomisation

2. First new neurological event or death over the first 12 months after randomisation

3. Neurological IRIS events over the first 6 months after randomisation

4. New AIDS-defining event or death over the first 12 months after randomisation

5. HIV-associated malignancy by 12 months from randomisation

6. Use of open-label corticosteroid treatment for any reason over the first 12 months after randomisation

7. Requirement for shunt surgery by 12 months

8. Any serious adverse events reported by 12 months from randomisation

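### Every adverse event comparison runs to 12 months and none is limited to the 6 to 8 weeks of study drug, so an excess of serious adverse events on the drug is diluted

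*SAP article*

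**What the plan says.** The eighth secondary endpoint (SAP, Secondary endpoints) is "Any serious adverse events reported by 12 months from randomisation". The section that analyses it is headed "Adverse events until 12 months" and names no other window. Its rule for the between-arm test is: "The number of patients with any serious adverse event will be summarised and compared between the two treatment arms based on the chi-squared test", with Fisher's exact test when an expected count is below one. The number of SAE episodes per patient is also compared, informally, by a quasi-Poisson model with treatment as the only covariate. Specific event types are described without a formal comparison.

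Tables 6a and 7 to 10 show, by arm, all SAEs, SAEs judged related to study drug, clinical grade 3 and 4 events, events leading to interruption of TB or antiretroviral treatment, and laboratory abnormalities. Each table has columns for patients and for episodes. None is restricted to time on study drug. Table 6b, which is not by arm, lists causing death as one of the reasons an event is serious.

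On exposure, the section Structure and status of trial says that grade 1 participants "received a 6-week tapering course of study drug" and that grade 2 and 3 participants "received an 8-week tapering course of study drug". The background section cites "mortality approaching 50% in people living with HIV".

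**The concern.** The drug is taken for a small part of the period over which harm is compared. The formal test asks only whether a patient had at least one SAE by 12 months. A patient with an SAE in week 3 and a patient whose first SAE is a death in month 5 contribute equally to it. Disease events and deaths after the course add patients to both arms. They also convert patients who were SAE-free on treatment into patients with an SAE, which removes part of any difference that arose on the drug. This happens even when survival and follow-up are identical between arms.

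The same section on trial structure lists adverse events considered related to dexamethasone among the key follow-up outcomes. Most other event outcomes in the SAP have some resolution in time: survival and secondary outcomes 2 to 7 are estimated at 3, 6 and 12 months, and IRIS has its own 6-month window. The adverse event comparisons have none. At stake is whether the randomised SAE comparison could show an excess confined to the weeks on treatment.

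**Working it through.** The SAP states no rate, effect size or power for the SAE comparison, so there is no figure of its own to reproduce.

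**Inputs from the SAP**
- Study drug for 42 or 56 days: 42/365 = 11.5% and 56/365 = 15.3% of the window.
- 520 enrolled ("the predefined sample size of 520 adults with TBM and HIV co-infection had been enrolled").
- Test on patients with at least one SAE by 12 months.
- Causing death is a seriousness criterion.

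**Assumptions**
- 260 per arm (520/2; the allocation ratio is not stated in the SAP).
- Two-sided 5% level; losses ignored (the SAP expects under 5%).
- p0 = proportion with an SAE on placebo during the scheduled course; p0 + d = the same on dexamethasone.
- q = chance of a first SAE after the course among patients still SAE-free, equal in both arms.

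**Step 1, dilution.** The 12-month proportion is p + (1 − p)q. The difference between arms is therefore [(p0 + d) + (1 − p0 − d)q] − [p0 + (1 − p0)q] = d(1 − q).

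**Step 2, power.** For proportions a and b with mean m and n = 260, power = Φ((|b − a| − 1.96·SE0)/SE1), where SE0 = √(2m(1 − m)/n) and SE1 = √((a(1 − a) + b(1 − b))/n).

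- On drug, 20% v 30%: SE0 = 0.0380, SE1 = 0.0377, and Φ((0.10 − 0.0744)/0.0377) = 0.75.
- At 12 months with q = 0.3, 44% v 51%: SE0 = 0.0438, SE1 = 0.0437, and Φ((0.07 − 0.0858)/0.0437) = 0.36.

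| Comparison | Placebo | Dexamethasone | Difference (points) | Risk ratio | Power |
|---|---|---|---|---|---|
| On drug | 20% | 30% | 10 | 1.50 | 75% |
| 12 months, q = 0.1 | 28% | 37% | 9 | 1.32 | 59% |
| q = 0.2 | 36% | 44% | 8 | 1.22 | 46% |
| q = 0.3 | 44% | 51% | 7 | 1.16 | 36% |
| q = 0.4 | 52% | 58% | 6 | 1.12 | 28% |
| q = 0.5 | 60% | 65% | 5 | 1.08 | 22% |
| q = 0.6 | 68% | 72% | 4 | 1.06 | 17% |

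**Step 3, sensitivity to the timing of SAEs.** If mortality is near 50% and every death is recorded as an SAE, the 12-month placebo total is about 50% or more. Fixing that total gives q = (total − p0)/(1 − p0). With d = 12 points:

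| p0 | Power on drug | 12-month power, total 50% | Total 60% | Total 70% |
|---|---|---|---|---|
| 20% | 88% | 40% | 29% | 21% |
| 30% | 82% | 50% | 37% | 26% |
| 40% | 79% | 63% | 48% | 34% |

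The loss is smaller when more of the SAEs come early. The mildest case in this table has q = (0.50 − 0.40)/0.60 = 0.17. With p0 = 40%, d = 12 and q = 0.1, power falls only from 79% to 69%.

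**Check.** A simulated chi-squared test without continuity correction (4,000 runs) gave 0.880 against 0.879 for 20% v 32%, and 0.400 against 0.403 for 50% v 57.5%.

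**The case against.** The case for the plan has several parts.

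- **The analysis matches the endpoint.** Endpoint 8 is defined to 12 months and is analysed to 12 months. The longer window preserves the randomised comparison and can catch delayed harm. This stands. A reader might infer that the 12-month comparison is wrong or should be displaced, and the SAP does not support that. The gap is that no exposure-period comparison stands beside it.
- **Episodes are also counted.** The quasi-Poisson model and the episode columns distinguish a patient with a week-3 SAE and a later fatal SAE from one with the fatal SAE only. This stands as partial mitigation. The comparison is labelled informal, and it also pools on-drug and later episodes.
- **Table 7 targets drug harm.** A reader might set Table 7 aside as not a randomised comparison. That would be wrong: the trial is double-blind, and relatedness attributed under blinding and compared by randomised arm is a classification of the outcome. Table 7 should filter out many later disease events. It still runs to 12 months and depends on causality calls, which are difficult when a drug effect can resemble a complication of TBM or HIV.
- **Early harm may show elsewhere.** Survival and secondary outcomes 2 to 7 are reported at 3 months, close to the end of dosing. This stands for those outcomes, but not for SAEs, graded events or laboratory abnormalities.
- **The size is assumed.** This stands in full. A reader might infer that on-drug harm is swamped, or that the test sits near its ceiling. The SAP gives neither SAE rates nor the timing of SAEs and deaths, so neither statement can be derived from it.

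**Conclusion.** The gap is real. All by-arm adverse event comparisons cover 12 months, the drug is scheduled for 6 or 8 weeks, and no comparison is limited to exposure. The direction of the effect follows from the arithmetic: for any q above zero that is equal in both arms, the any-SAE test sees d(1 − q) instead of d.

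The size is conditional. With 260 per arm and 20% v 30% on drug, power of about 75% falls to about 59%, 36% or 17% for q of 0.1, 0.3 or 0.6. The loss is modest if most first SAEs occur during the course and severe if many occur after it. These figures rest on assumed on-drug rates, 1:1 allocation and a later risk that is the same in both arms. The episode model and Table 7 reduce the problem but do not remove it.

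This is an inexpensive improvement to the safety analysis. It does not invalidate the plan.

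**What to change.** Keep the 12-month any-SAE comparison as the prespecified analysis of endpoint 8. Before unblinding, add to the adverse event section a companion by-arm version of Tables 6a, 7, 8 and 10, with these features:

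- all randomised participants, in the arm assigned;
- events with onset from day 0 to the end of the scheduled course (day 42 for MRC grade I, day 56 for grades II and III), regardless of when a participant actually stopped;
- one fixed lag after that date, with its length stated in the SAP;
- a label marking these comparisons as supportive.

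Defining the window by schedule keeps it from depending on what happened after randomisation. The cost is a paragraph of SAP wording and a filter on onset dates, which the trial should already hold. The downside is one more set of tables and one more secondary safety comparison. If the window and lag were chosen after unblinding, the comparison would be post hoc.

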Anti-tuberculosis drug resistance ^ # ^ - Multi-drug resistant or rifampicin mono-resistant - Isoniazid resistant non-MDR - Pre-XDR - XDR - No or other resistance	XX XX XX XX XX	XX (XX%) XX (XX%) XX (XX%) XX (XX%) XX (XX%)	XX XX XX XX XX	X.XX X.XX X.XX X.XX X.XX	X.XX
ART status at enrolment - ART naïve - ≤3 months of ART - >3 months of ART	XX/XX XX/XX XX/XX	XX/XX XX/XX XX/XX	X.XX (X.XX, X.XX) X.XX (X.XX, X.XX) X.XX (X.XX, X.XX)	X.XX X.XX X.XX	X.XX
Enrolment CD4 count (per mm ^3^) - <50 - 51–100 - 101–200 - >200	XX/XX XX/XX XX/XX XX/XX	XX/XX XX/XX XX/XX XX/XX	X.XX (X.XX, X.XX) X.XX (X.XX, X.XX) X.XX (X.XX, X.XX) X.XX (X.XX, X.XX)	X.XX X.XX X.XX X.XX	X.XX

*Heterogeneity will be tested with a Cox regression model that includes an interaction between treatment effect and subgroup.
^#^Results will be given for sub-group with positive mycobacterial culture on baseline CSF. Pre-XDR and XDR are defined following World Health Organisation definitions
^
11
^. The primary endpoint will be overall survival, i.e., time from randomisation to death, over the first 12 months of follow-up. This table reports the results from the Cox proportional hazards regression model. The primary effect measure will be the resulting hazard ratio comparing dexamethasone vs. placebo with a corresponding two-sided 95% confidence interval. In these subgroup analyses, a separate Cox model will be fitted for each value of the subgroup. The "Test for heterogeneity" will be based on the likelihood ratio test that includes subgroup as covariate and compares the models with subgroup as main effect only and with subgroup as treatment effect modifier, with TBM MRC severity grade at enrolment (I, II, or III) as covariates. ART=antiretroviral therapy. MRC=Modified Research Council. TBM=tuberculous meningitis. XDR=extensively drug resistant.

Survivors known to be alive at 12 months will be censored at that time-point and subjects who withdrew or were lost to follow-up before 12 months will be censored at the date they were last known to be alive. Subjects who withdrew or were lost to follow-up before 12 months are estimated to be less than 5% of enrolled participants.

The homogeneity of the treatment effect on overall survival across subgroups will be assessed by formal tests of interaction between treatment and the following pre-defined grouping variables: TBM MRC severity grade at enrolment (I, II, or III), diagnostic category (definite, probable, possible),

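### The comparison of serious adverse event episodes states no follow-up time and mixes deaths with non-fatal toxicity

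*SAP article*

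**What the plan says.** The SAP article makes two overall comparisons of SAEs, both in the section on adverse events until 12 months.

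- **Patients:** "The number of patients with any serious adverse event will be summarised and compared between the two treatment arms based on the chi-squared test", with Fisher's exact test when an expected cell count is very small.
- **Episodes:** the number of SAE episodes per patient is "informally compared based on a quasi-Poisson regression model with treatment as the only covariate".

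The footnote to Table 6a takes percentages over all patients in the arm. No offset, person-time or competing-risk rule is stated for SAEs. The first column of Table 6b is for events that cause death, so a fatal event is an SAE. The full SAE definition is left to the protocol.

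Elsewhere the plan does handle time at risk. The neurological IRIS rate is "the number of IRIS events divided by the observed person-time of follow-up in each treatment group", and death is a competing risk for secondary outcomes 3, 5, 6 and 7. SAEs are secondary endpoint 8 and get neither treatment.

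The background section describes TBM "with mortality approaching 50% in people living with HIV". Withdrawals and losses before 12 months "are estimated to be less than 5% of enrolled participants".

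**The concern.** A patient who dies in the first month has little time in which to have further SAEs, and a survivor has twelve months. With mortality near 50% and other loss below 5%, death is what makes observation time unequal. Death is also the primary endpoint, so if dexamethasone changes survival in either direction, time at risk differs between the arms.

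Two effects then act on the episode count. Longer survival adds non-fatal episodes to the better-surviving arm, while each death adds a fatal episode to the other arm. A model with treatment as the only covariate returns one ratio that contains both. The same non-fatal toxicity per month could show as an excess, a deficit or no difference. At stake is whether a reader weighing benefit against harm can tell if an SAE ratio reflects toxicity or mortality.

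**Working it through.** The plan gives no figure for this comparison, so there is none to reproduce. The check asks what the episode ratio would be if the two arms had the **same** non-fatal SAE rate.

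**Inputs from the document:** mortality approaching 50%; loss before 12 months under 5% (ignored below); fatal events count as SAEs (Table 6b).

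**Assumptions:** 12-month mortality m of 45% v 36%, 50% v 40% or 45% v 40%; deaths front-loaded (Weibull shape 0.5) or at constant hazard; r = 0.5 to 3 non-fatal SAEs per patient-year; each death adds one episode.

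**Step 1. Mean follow-up F, in years.** Let λ = −ln(1 − m).
- Front-loaded deaths: F = 2[1 − (1 + λ)(1 − m)]/λ².
- Constant hazard: F = m/λ.

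For m = 0.45, λ = 0.598. The front-loaded F is 2 × [1 − 1.598 × 0.55]/0.357 = 0.678 years, or 8.14 months.

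**Step 2. Non-fatal episodes only.** The expected count per patient is rF, so r cancels and the ratio is F₁/F₀, where arm 1 survives better.

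| Mortality | F₀ v F₁, front-loaded (months) | Ratio | Ratio, constant hazard |
|---|---|---|---|
| 45% v 36% | 8.14 v 8.96 | 1.10 | 1.07 |
| 50% v 40% | 7.66 v 8.60 | 1.12 | 1.09 |
| 45% v 40% | 8.14 v 8.60 | 1.06 | 1.04 |

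**Step 3. Fatal events included, as Table 6b implies.** The ratio is (rF₁ + m₁)/(rF₀ + m₀). Front-loaded deaths:

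| Mortality | r = 0.5 | r = 1 | r = 2 | r = 3 |
|---|---|---|---|---|
| 45% v 36% | 0.93 | 0.98 | 1.03 | 1.05 |
| 50% v 40% | 0.93 | 0.98 | 1.03 | 1.06 |
| 45% v 40% | 0.96 | 0.99 | 1.01 | 1.03 |

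Under constant hazard the lowest value is 0.92 (50% v 40%, r = 0.5). The ratio crosses 1 at r = (m₀ − m₁)/(F₁ − F₀). For 45% v 36% with front-loaded deaths that is 0.09/(0.747 − 0.678), about 1.3 per patient-year.

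**Step 4. Any SAE, fatal events included.** The proportion is 1 − (1 − m)e^(−r). For 45% v 36% and r = 1 it is 79.8% v 76.5%, lower in the better-surviving arm. That holds for every r, because 1 − m is larger in that arm.

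**Step 5. What an offset does.**
- Non-fatal episodes at a constant SAE rate: the ratio returns to 1.00.
- Non-fatal episodes front-loaded with shape 0.5: the expected count is r·m/λ, so the raw ratios become 1.07, 1.09 and 1.04. Dividing by the follow-up ratios 1.10, 1.12 and 1.06 leaves 0.97, 0.97 and 0.98, a slight over-correction.
- All episodes with deaths included, 45% v 36%: dividing the Step 3 ratios by 1.10 gives 0.84 (r = 0.5) to 0.95 (r = 3), further from 1 at the lower rates than with no offset.

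**The case against.** The strongest defence has four parts.

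1. **The episode comparison is labelled informal, and no decision rule rests on it.** This stands and limits the weight of the point. Neurological events, IRIS, malignancy, open-label steroid use and shunt surgery also have their own time-to-event analyses.
2. **An offset is not a covariate, so the wording does not rule one out.** True, but none is specified, while person-time is written out for IRIS.
3. **The chi-squared test needs no repair.** This largely stands. With under 5% lost, the crude proportion with an SAE by 12 months is close to the Aalen-Johansen estimate at 12 months, and it is a legitimate comparison of all randomised patients. Replacing it would change little.
4. **The SAE definition is in the protocol, which is not shown.** This is a real limit. If deaths are kept out of SAE reporting there, the ratios in Step 2 apply rather than those in Step 3.

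A reader might infer something stronger: that the arm with fewer deaths will look less safe simply because its patients live longer. The document does not support that. Fatal events are themselves SAEs, so the any-SAE proportion moves in favour of the better-surviving arm (Step 4). The episode ratio goes against that arm only when non-fatal SAEs are frequent, above about 1.3 per patient-year in the 45% v 36% case, and then by a few per cent. The plan gives no SAE rate, so no direction can be claimed.

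**Conclusion.** The point holds as a fault of specification and interpretation. The planned episode ratio states no follow-up time and combines mortality with non-fatal toxicity. With equal non-fatal rates, the non-fatal component is distorted by about 4% to 12% against the better-surviving arm. The combined ratio runs from about 0.92 to 1.06, with no fixed direction.

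These sizes rest on assumed mortality pairs, event timing and SAE rates; only the mortality level near 50% and the loss below 5% come from the document. Larger survival effects widen the ranges: with 50% placebo mortality and hazard ratios of 0.6 to 0.8, they are 1.06 to 1.19 for non-fatal episodes and 0.87 to 1.09 with deaths included. The distortion is modest and the comparison informal. The primary result is untouched, and the any-SAE test can stay.

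**What to change.** In the section on adverse events until 12 months:

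- Report fatal and non-fatal SAEs separately by arm. Table 6b, as planned, is not split by arm.
- Fit the quasi-Poisson model to **non-fatal** SAE episodes, with an offset of log(time from randomisation to the earliest of death, withdrawal, last contact or 12 months), and show it beside the planned raw counts.
- State that the offset is not applied to counts that include fatal events.
- Keep the chi-squared or Fisher test of any SAE, and describe it as a 12-month proportion that includes fatal events.
- Because a rate assumes roughly constant risk and the offset over-corrects slightly if SAEs come early, also give non-fatal rates for the study-drug period and for the time afterwards.

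The cost is a few sentences in the SAP and a few lines of code. The dates of randomisation, death and last contact are already needed for the primary analysis.
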